#### 3.4.2 Sample size re-assessment

Due to the limitation of available data on the cure rate of AS+MQ in the target population and to the uncertainty regarding the expected rate of withdrawals, an interim analysis will be performed solely for sample size re-assessment. This analysis will be carried-out when approximately half of the patients originally planned (i.e. ~525 patients) are randomized and have reached the Day 63 evaluation.

This analysis will be performed for checking:

- the overall rate of patients withdrawing from the study considering all the possible reasons;
- the proportion of non evaluable PCR;
- the overall 63-day PCR corrected cure rate.

These evaluations will be carried-out in each of the two primary populations (i.e. modified ITT and PP populations) by the Data Monitoring Board. The sample size will be recomputed based on these findings and changed accordingly, if an increase is needed (i.e. no downsizing will be implemented). As a general rule, the Data Monitoring Board will base the above specified evaluations on blind data.

The sample size resulting from this assessment (either if necessitating an adjustment or not) will not be communicated to the Investigators so as not to reveal any information on the primary outcome (rate of cure) of the study.

The method for performing this analysis could be based on the papers by A.L. Gould and J Herson and J. Wittes. However, such methods apply to superiority studies and therefore need to be adapted for the non-inferiority case. All details of this interim analysis will be provided in the Statistical Analysis Plan (or a separate document) that will be finalized before starting any interim analysis.

#### **MODIFICATION:**

##### **Page 28: Section 5 Patient Withdrawal Criteria**

**Reason for modification:** Criterion number 3 specified only day 0, but actually persistent vomiting is relevant at any day.

Need to address the modified intention-to-treat population.

*Therefore:*

During the study, the following conditions are reasons for excluding the patients from further participation in the trial:

1. Use of antimalarial drugs outside of the study protocol.
2. Withdrawal of informed consent.
3. Lost to follow-up: patients who fail to attend a follow-up visit and are unable to be located within 48 hours on Days 1-14 or for more than 2 subsequent visits between Days 15-63.
4. Patient's request to discontinue for any reason.
5. At the investigator's request for safety reasons

*is modified as follows*

During the study, the following conditions are reasons for stopping the study treatment and/or for excluding the patients from further efficacy assessments.

- 1 Any treatment failure (including early failures).
- 2 Use of antimalarial drugs (or antibiotics with antimalarial activity) outside of the study protocol.
- 3 Persistent vomiting of study drugs (at least twice the same dose).
- 4 Failure to complete the study treatment.
- 5 Withdrawal of informed consent.
- 6 Investigator's request for safety reason.
- 7 Lost to follow-up: patients cannot be located by Day 63.

Patients with one or more of the conditions listed above will have to be followed-up for the safety assessments until day 63. These patients will be considered failures in the intention-to-treat population, will be considered partly failures and partly excluded in the modified intention-to-treat analysis and, with exclusion of condition 1, they will be excluded from the Per Protocol population (see sections 8.1 and 8.2).

**Modified Intention-to-Treat (modified ITT) Population.** Defined as the ITT population with the exclusion of the lost-to-follow-up patients before Day 63 for unknown reasons (non informative drop-outs). More specifically, patients withdrawing from the study for reason 7 (see section 5) will be excluded, while all other withdrawals will be counted as failures (these reasons might be potentially considered correlated with lack of efficacy, i.e. are referred to as informative drop-outs). The patients for whom the PCR is not interpretable or missing will be assigned the result “recrudescence” or “re-infection” according to the ratio between these outcomes which was observed among the evaluable PCRs within each treatment group. This rule about PCR will be applied for the primary analysis. For all analyses for which the knowledge of the outcome is needed for each patient individually (for example, the Breslow Day test or the logistic regression or the analyses where a baseline covariate is needed), different scenarios will be considered, i.e. the most two extreme ones of considering all patients with not interpretable or missing PCRs as failures or as successes and the intermediate one of excluding them all.

**Per-Protocol (PP) Population.** Defined as all randomized patients who will be eligible according to the study protocol, will receive at least 80% of the study medication, will have the Day 63 assessment, will not take other anti-malarial drugs and, in case of the presence of asexual parasite stages on thick or thin blood smears, will have an evaluable PCR. The protocol violations listed below will also be considered reasons for excluding the patients from this population:

- failure to attend visits between Days 0 – 2 and unable to be located within 6 hours of the scheduled visits;

failure to attend two consecutive visits between Days 3 and 63 (every visit between Day 3 and Day 56 must take place within 48 hours of the scheduled time; visit at Day 63 can occur minus 1 or plus 7 days of the scheduled visit)..

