#### 8.2.1 Analysis for showing non-inferiority of Artekin vs AS+MQ

The primary analysis will be based on a 97.5% (one-sided) Confidence Interval (CI) computed on the difference between the 63-day PCR corrected cure rates of the test and the reference treatments, respectively.

In order to claim that Artekin is non-inferior to AS+MQ the lower limit of the CI must be  $> -0.05$  in both the modified ITT and the Per Protocol populations. The analysis on the more pure ITT population (see section 8.1) will be used for investigating robustness of results (see below).

The method for computing the CI will be specified in the SAP.

For computing the PCR-corrected cure rate, the patients who are diagnosed to be re-infected will be counted as successes (they have to be terminated on that day of follow-up) while the patients for whom the PCR is not interpretable or the sample is unavailable will be treated differently depending on the population considered (see section 8.1).

Robust analysis will be performed on the more pure ITT population by applying the following methods:

1. All patients who withdrew from the study for one of the reasons listed in section 5 (from 1 to 7) will be evaluated as failures as well as the patients for whom the PCR is not interpretable or missing
2. Patients who withdrew from the study for reasons that cannot be considered uncorrelated with the study treatments (i.e. reasons from 1 to 6) will be counted as failures (i.e. assigned with a 0 value), while the patients prematurely interrupting the study for reason

7 (lost to follow-up) will be assigned with a value ranging from 0.5 to 0.9 (imputation of a postulated probability of success for the patients for whom the treatment outcome could not be evaluated). Finally, all cured patients (or with re-infection by PCR) will be assigned with a 1 and this transformed endpoint will be summarized in terms of means and corresponding standard errors by treatment group. This analysis will be repeated for taking into account different ways of treating the patients with a non-interpretable or missing PCR (from failure to exclusion).

3. The analysis of the 63-day PCR corrected cure rates will be performed by means of the survival analysis techniques, where the non informative lost-to-follow-up patients (i.e. unable to locate the patient) and the patients with a non-interpretable or missing PCR will be censored at the time of exiting the study.

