#### 8.2.2 Historical comparisons

In order to compare the study results with the historical ones, the criteria described in the WHO document ("Assessment and Monitoring of Antimalarial Drug Efficacy for the Treatment of Uncomplicated Falciparum Malaria – 2003". See chapter 7, section 7.3) will be used. Therefore, the failure rates will be estimated through survival analysis (Kaplan-Meier method) in each treatment group individually considered. This analysis will be carried-out in the per-protocol population and the results obtained in each of the two treatment groups will be judged against the threshold of 90% (there is consensus among the malaria experts in recognising that the threshold of 90% should be considered as a "rule of thumb" for judging efficacy).

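### Sections 5 and 8.1 contradict each other on whether patients who fail or are re-infected before Day 63 belong to the Per Protocol population, and on which treatment-completion rule applies

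*Supplement*

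**What the plan says.** All references are to the current (amended) text in the protocol amendment.

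- **Section 8.1, PP definition.** Membership is a list of joint requirements. Beyond eligibility, the patient "will receive at least 80% of the study medication, will have the Day 63 assessment, will not take other anti-malarial drugs". An evaluable PCR is needed where parasites are present, and two consecutive missed visits between Days 3 and 63 exclude.
- **Section 5, withdrawal criteria.** Condition 1 is "Any treatment failure (including early failures"), condition 2 is "Use of antimalarial drugs (or antibiotics with antimalarial activity) outside of the study protocol", and condition 4 is "Failure to complete the study treatment". Any of these can end further efficacy assessment. Patients who meet a condition are followed for safety to Day 63 and, "with exclusion of condition 1, they will be excluded from the Per Protocol population".
- **Section 8.2.1.** Re-infected patients count as successes, but "they have to be terminated on that day of follow-up". Non-inferiority must be shown in both modified ITT (mITT) and PP.
- **Section 8.2.2.** Kaplan-Meier failure rates in each arm are judged against 90%: "This analysis will be carried-out in the per-protocol population".
- **Section 3.4.2.** The interim re-assessment looks at withdrawal, non-evaluable PCR and overall cure rate in mITT and PP.

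**The concern.** Section 5 and section 8.1 cannot both be applied as written.

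Section 5 lifts one ground for exclusion, namely being a treatment failure. It does not waive the entry requirements of 8.1. A patient who fails on, say, Day 28 has no further efficacy assessments, so it is unclear whether a safety contact at Day 63 counts as the required assessment. If that patient is then re-treated, the 8.1 bar on other antimalarials may exclude the patient as well. An early failure whose treatment is stopped may also fall below 80% of medication, or meet condition 4, which section 5 does not exempt.

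Two people could therefore build different PP datasets from the same text. One keeps all failures. The other drops most failures that occur before Day 63, which are the events that the endpoint exists to count. The second dataset would make the PP non-inferiority test uninformative and would flatter both arms against the 90% threshold.

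**Working it through.** **1. The two rules side by side**

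| Patient | Section 5 | Section 8.1 read literally |
|---|---|---|
| Failure before Day 63, full treatment taken | In PP (condition 1 exempt) | Out, unless a safety contact counts as the Day 63 assessment and any re-treatment does not count as another antimalarial |
| Early failure, treatment stopped | Exempt under condition 1, excluded under condition 4; no precedence given | Out if below 80% of medication, or for the reasons above |
| Re-infection before Day 63 (a success) | In, if read as a failure before PCR correction | No Day 63 efficacy assessment, so out |
| No failure, 80% to under 100% of treatment | Out (condition 4) | In |
| Failure first detected at Day 63 | In | In |

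**2. The plan's own PP figure**

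Inputs from section 3.4.1: 700 and 350 patients, 20% PP attrition, 95% PP cure rate, margin 0.05, one-sided alpha 0.025. PP size is 0.8 × 700 = 560 and 0.8 × 350 = 280.

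- SE = √[0.95 × 0.05 × (1/280 + 1/560)] = 0.01595
- Continuity correction = 0.5 × (1/280 + 1/560) = 0.00268
- Power = Φ[(0.05 − 0.00268)/0.01595 − 1.96] = Φ(1.007) = 84.3%; the plan states 84%

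The same formula for mITT (665 and 332.5 patients, 93%) gives 79.6%, against the stated approximate 80%. Other treatments of the null variance, with the continuity correction, give 76.8% or 86.7% for PP, so this is the variant that matches.

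Expected PP failures are 0.05 × 560 + 0.05 × 280 = 28 + 14 = 42 of 840. The 84% thus presupposes that failures are in PP. With all of them removed, the cure rate would be 100% in each arm by construction.

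**3. Effect of a literal 8.1**

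Let f be the share of failures that 8.1 removes. The documents do not give f, so the full range from 0 to 1 is shown. With true cure rate p, the observed rate is p / [p + (1 − p)(1 − f)]. The lower limit is the observed difference minus 1.96 × SE (Wald), using the patients who remain. The reference arm has the planned 95%; the test-arm rates of 90% and 85% are illustrations.

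| f | Reference observed | Test, true 90%: observed (lower limit) | Test, true 85%: observed (lower limit) |
|---|---|---|---|
| 0 | 95.0% | 90.0% (−0.086) | 85.0% (−0.139) |
| 0.25 | 96.2% | 92.3% (−0.071) | 88.3% (−0.114) |
| 0.50 | 97.4% | 94.7% (−0.054) | 91.9% (−0.086) |
| 0.75 | 98.7% | 97.3% (−0.034, passes) | 95.8% (−0.052) |
| 1 | 100% | 100% (difference 0) | 100% (difference 0) |

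Worked entry, true 85%, f = 0.5: 0.85 / (0.85 + 0.15 × 0.5) = 0.85 / 0.925 = 91.9%.

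**4. What mITT does**

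Under 8.1, mITT counts every withdrawal except reason 7 as a failure, so the PP wording cannot affect it. At 665 and 332 patients, with a Wald limit, the probability of passing in mITT is about 0.000001 when the true rates are 85% and 95%, and about 2% when they are 90% and 95%.

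**The case against.** A reader of 8.1 alone might infer that the plan removes the failures from PP, that PP cure rates will be close to 100%, and that an inferior drug would be declared non-inferior. The documents do not support that reading, for these reasons.

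- Section 5 states the exception for failures and refers to 8.1 and 8.2. The 95% PP cure rate, the evaluable-PCR clause and the Kaplan-Meier failure rates in PP all presume failures in that population. The intent is clear. This stands.
- Non-inferiority requires both populations. mITT retains the failures, so a high pass rate in a literal PP analysis is not a false-claim rate for the trial. This also stands. What would be lost is PP as an independent check.
- Re-treatment provisions are not shown, and condition 2 speaks only of antimalarials outside the protocol. Whether protocol-directed re-treatment would breach 8.1 is open. This stands, and it is part of the ambiguity.
- Re-infections may be covered by condition 1, because section 2.1 describes them as treatment failures identified by PCR as new infections. Likewise, 80% may be meant as the definition of completion. Both are possible readings, but neither is written down.
- The 90% threshold is described as a rule of thumb and is separate from the non-inferiority claim. That limits the consequence there. However, this comparison uses PP only and has no mITT safeguard.
- The SAP and full protocol are not shown and may settle the rule. The two amended sections would still conflict.

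**Conclusion.** The contradiction is real and should be resolved before any PP dataset is built, including the one for the interim re-assessment. Sections 5 and 8.1 give incompatible membership rules for failures and re-infections before Day 63, for early failures who also did not complete treatment, and for patients who took 80% or more but not all of their treatment.

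The size of any bias depends on which rule is programmed and on f. If section 5 governs, no planned figure changes: 840 PP patients, about 42 failures, power 84.3%. If 8.1 is applied literally, the PP cure rates rise with f. In the illustrations, half the failures removed lifts a true 85% above the 90% threshold, and three quarters removed lets a drug that is truly 5 points worse pass the PP test. An inflated PP rate would also lead the re-assessment to understate the variance: at the planned 95%, f = 0.5 gives 97.4%, and p(1 − p) falls from 0.0475 to about 0.025. The mITT input to the re-assessment is unaffected.

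The finding is an inconsistency that could bias PP. It does not show that failures are certain to be excluded, or that the trial's type I error is lost.

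**What to change.** In section 8.1:

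1. State that patients with a treatment failure or a re-infection, with evaluable PCR, at any time up to Day 63 belong to PP without needing a Day 63 assessment.
2. Apply the dosing, visit-attendance and other-antimalarial conditions only up to the day of that event.
3. Reconcile section 5 condition 4 with the 80% rule so that one completion criterion defines PP, and say how an early failure who also meets condition 4 is classified. Which criterion to adopt is for the sponsor to decide.

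Carry the same wording into the SAP. The cost is a few sentences; no patients, visits or procedures are added, and the stated PP power is unchanged.

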## **MODIFICATION:**

### **Page 32: Section 8.2 Efficacy: primary analysis**

**Reason for modification:** There are several reasons for proposing this change:

- To specify statistical techniques that are suited for the two different objectives of proving non-inferiority on one side and comparing the study results with the historical ones on the other side (as mentioned at point 3 above, in the former case the primary focus is on bias and variability while in the latter it is on reproducibility of the experimental setting).

- To consider a method for assigning a value to the missing or non-interpretable PCR analyses in the modified intention-to-treat population.
- To provide more details on additional analyses, such as the robust analysis and the evaluation of homogeneity across centres, that are very important for the interpretation of the study results but were not provided in the original version of the protocol.
- To harmonize this study with the other phase III study of the Artekin project currently conducted in Africa.

*Therefore:*

The primary analysis will be based on a 97.5% (one-sided) Confidence Interval (CI) computed on the difference between the 63-day PCR corrected cure rates of the test and the reference treatments, respectively.

In order to claim that DHA+PPQ is efficacious, the lower limit of the CI must be  $> -0.05$  and the point estimate for the 63-day PCR corrected cure rate of DHA+PPQ must be  $> 0.90$ , in both the ITT and the Evaluable populations.

The method for computing the CI will be specified in the SAP.

For computing the PCR-corrected cure rate, the following rules will be applied:

- the patients who are diagnosed to be re-infected are counted as successes (they have to be terminated on that day of follow-up);
- the patients for whom the PCR is not interpretable or is missing are counted as failures in the ITT population, while they are excluded from the Evaluable population. The proportion of these patients is less than 10% of patients who experienced a recurrent parasitaemia (i.e. those in whom the PCR evaluation is performed).

*is modified as follows:*

#### 8.2.1 Analysis for showing non-inferiority of Artekin vs AS+MQ

The primary analysis will be based on a 97.5% (one-sided) Confidence Interval (CI) computed on the difference between the 63-day PCR corrected cure rates of the test and the reference treatments, respectively.

In order to claim that Artekin is non-inferior to AS+MQ the lower limit of the CI must be  $> -0.05$  in both the modified ITT and the Per Protocol populations. The analysis on the more pure ITT population (see section 8.1) will be used for investigating robustness of results (see below).

The method for computing the CI will be specified in the SAP.

For computing the PCR-corrected cure rate, the patients who are diagnosed to be re-infected will be counted as successes (they have to be terminated on that day of follow-up) while the patients for whom the PCR is not interpretable or the sample is unavailable will be treated differently depending on the population considered (see section 8.1).

Robust analysis will be performed on the more pure ITT population by applying the following methods:

1. All patients who withdrew from the study for one of the reasons listed in section 5 (from 1 to 7) will be evaluated as failures as well as the patients for whom the PCR is not interpretable or missing
2. Patients who withdrew from the study for reasons that cannot be considered uncorrelated with the study treatments (i.e. reasons from 1 to 6) will be counted as failures (i.e. assigned with a 0 value), while the patients prematurely interrupting the study for reason

7 (lost to follow-up) will be assigned with a value ranging from 0.5 to 0.9 (imputation of a postulated probability of success for the patients for whom the treatment outcome could not be evaluated). Finally, all cured patients (or with re-infection by PCR) will be assigned with a 1 and this transformed endpoint will be summarized in terms of means and corresponding standard errors by treatment group. This analysis will be repeated for taking into account different ways of treating the patients with a non-interpretable or missing PCR (from failure to exclusion).

3. The analysis of the 63-day PCR corrected cure rates will be performed by means of the survival analysis techniques, where the non informative lost-to-follow-up patients (i.e. unable to locate the patient) and the patients with a non-interpretable or missing PCR will be censored at the time of exiting the study.

The impact of these strategies on the conclusions will be carefully evaluated and discussed.

The Breslow Day test or logistic regression will be used to evaluate homogeneity across centers. In this respect, each center would need to have at least two failures for each treatment in order for large sample chi-square approximations to be applicable. If this type of condition does not apply, exact logistic regression will be used to address homogeneity across centers. In addition, if the sample sizes are sufficiently large within centers so that each treatment has at least five failures within each center, a confidence interval adjusted for centers as strata will be computed (see Koch and others, Statistics in Medicine, 1998).

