### 3.4.1 Sample Size Computation

The study is designed as a non-inferiority trial.

The level of the PCR-corrected cure rate at day 63 for Artesunate+Mefloquine has been estimated, through a literature search, to be in the range 92%-95% in the Intention-To-Treat (ITT) population. The opinion of physicians and experts in malaria treatment has been sought for defining the non-inferiority margin, and this has been set at 5%.

An unequal randomization with 2:1 structure was chosen because it assures a larger sample size for the DHA+PPQ group which provides the following advantages:

- a more precise estimate of the DHA+PPQ cure rate;
- a bigger sample for the integrated safety data base of DHA+PPQ, that renders more likely the elucidation of rare adverse reactions, if any.

From an ethical point of view, this choice appears reasonable in view of the previous data on DHA+PPQ, in terms of both safety and efficacy.

Sample size was initially (see original version of the protocol) computed considering the original formulation of the primary objective, which required the use of a simulation (details are provided in a separate document - see Sample Size and Design Justification for The Pivotal Clinical Trials of Dihydroartemisinin+ Piperaquine).

Having divided the two criteria of non-inferiority and comparison of study results with historical ones, power has been recomputed for each of the two objectives as described below.

For the non-inferiority analysis, the clinical and statistical specifications for the sample size computations are as follows:

- Primary endpoint = PCR-corrected cure rate at day 63.
- Primary analysis = based on 97.5% one-sided confidence intervals for the difference in cure rates.
- Alpha = 0.025 (one-sided).
- Power = 80%.
- Cure rate of Artesunate+Mefloquine in the pure ITT population = at least 92%.
- Non-inferiority margin for the difference (test-reference) = -0.05.
- Randomization: based on a 2 :1 allocation scheme (test : reference).
- Rate of patient attrition in the modified intention-to-treat population as compared to the pure ITT population (i.e. rate of non-informative withdrawals, i.e. reason number 7 of section 5) = 5%. Expected 63-day PCR corrected cure rate in this population = 93%.
- Rate of patient attrition in the Per Protocol Population as compared to the ITT population (i.e. rate of withdrawals for any reason and protocol violations) = 20%. Expected 63-day PCR corrected cure rate in this population = 95%.

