- Primary Analysis Populations = both the modified Intention To Treat (ITT) and the Per Protocol Populations.

With these assumptions, the sample size of 1050 patients (700 in the Artekin group and 350 in the AS+MQ group) provides a power of approximately 80% for the lower bound of a 97.5 one-sided confidence interval for the treatment difference being above -0.05 in the modified ITT and 84% for the same analysis in the Per Protocol population (for the power calculation both continuity correction and inequality of variances under the null hypotheses have been considered).

For the historical comparisons, the clinical and statistical specifications for the sample size computations are as follows:

- Anticipated population proportion of clinical failures = as high as 10%.
- Confidence level = 95% (two-sided interval).
- Precision = 5 percentage points.
- Rate of patient attrition in the Per Protocol Population as compared to the ITT population (i.e. rate of withdrawals for any reason and protocol violations) = 20%.

According to Annex 4 of the WHO document “Assessment and Monitoring of Antimalarial Drug Efficacy for the Treatment of Uncomplicated Falciparum Malaria – 2003”, a sample size of at least 175 patients would be required in each treatment group for estimating the proportion of clinical failures to within a 5 percentage point of the true value with 95% confidence.

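### No planned robustness analysis lets the outcome of patients lost to follow-up differ between arms, and Method 2 leaves out the uncertainty of the values it imputes

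*Supplement*

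**What the plan says.** The governing text is the amendment (Supplement); no SAP is shown.

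- **Modified ITT (section 8.1):** "Defined as the ITT population with the exclusion of the lost-to-follow-up patients before Day 63 for unknown reasons". Withdrawals for the other reasons in section 5 count as failures.
- **Per Protocol (section 8.1):** the Day 63 assessment is required. Section 5 confirms that every withdrawal condition except treatment failure leads to exclusion. Lost patients are therefore outside this population too.
- **Decision rule (section 8.2.1):** the lower confidence limit must lie above -0.05 in both populations.
- **Robustness (section 8.2.1), in the pure ITT population:**
  - Method 1 counts lost patients as failures in both arms.
  - Method 2 gives 0 to other withdrawals and 1 to cured or re-infected patients, while patients stopping for reason "7 (lost to follow-up) will be assigned with a value ranging from 0.5 to 0.9". The score is then "summarized in terms of means and corresponding standard errors by treatment group".
  - Method 3 is a survival analysis that censors lost patients at exit.
- **Missing or non-interpretable PCR:** Method 2 is repeated with these patients handled in ways from failure to exclusion. Section 8.1 adds all-failure, all-success and exclusion scenarios for analyses that need individual outcomes. None of these is described as differing by arm.

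**The concern.** Both co-primary analyses omit the same patients, so passing both says nothing about what happened to them. That question rests on the robustness analyses.

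In an open-label non-inferiority trial, the damaging possibility is that lost Artekin patients failed more often than lost AS+MQ patients. Method 1 applies one rule to both arms. Method 2 names a range without mentioning arm. Method 3 takes loss as non-informative. If Method 2 is run as it reads, with one value at a time for everyone, a conclusion that depends on a difference between the arms' lost patients would not be exposed.

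Method 2 also summarises a 0/v/1 score by its mean and standard error. Every lost patient then contributes exactly v, with no variation around it, although each real outcome is cure or failure. The stated output is means and standard errors by group, not the lower limit on which non-inferiority is decided.

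**Working it through.** **Inputs (section 3.4.1).** "Alpha = 0.025 (one-sided"); "Non-inferiority margin for the difference (test-reference) = -0.05"; "Randomization: based on a 2 :1 allocation scheme (test : reference"); "the sample size of 1050 patients (700 in the Artekin group and 350 in the AS+MQ group"); and for loss and cure in the modified ITT, "reason number 7 of section 5) = 5%. Expected 63-day PCR corrected cure rate in this population = 93"%. For Per Protocol, the plan gives 20% attrition and 95% cure.

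**Step 1: reproduce the plan's power.** Power = Φ((0.05 − c)/SE − 1.96), with c = (1/n1 + 1/n2)/2 and SE = √[p(1 − p)(1/n1 + 1/n2)].

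- Modified ITT, 665 + 332.5 at 93%: SE = 0.01714, c = 0.00226, power 79.6% (plan: approximately 80%).
- Per Protocol, 560 + 280 at 95%: SE = 0.01595, c = 0.00268, power 84.3% (plan: 84%).

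Both figures are reproduced, so the inputs are read as the plan meant them.

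**Step 2: Method 2 formulas.** Let L be the share lost, p the cure rate among observed patients and v the assigned value.

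- Arm mean: m = (1 − L)p + Lv.
- Variance of the score as written: (1 − L)p + Lv² − m².
- Variance if lost outcomes are binary with probability v: m(1 − m).
- Lower limit: difference − 1.96 × SE, with 700 and 350 patients.

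**Step 3: 93% observed cure in both arms, 5% lost in each.** The modified ITT gives 0 − 1.96 × 0.0171 = -0.034.

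| Artekin v | AS+MQ v | Difference | SE, score | Lower limit |
|---|---|---|---|---|
| 0 (Method 1) | 0 | 0 | 0.0210 | -0.041 |
| 0.5 | 0.5 | 0 | 0.0174 | -0.034 |
| 0.9 | 0.9 | 0 | 0.0163 | -0.032 |
| 0.5 | 0.9 | -0.020 | 0.0167 | **-0.053** |
| 0 | 1 | -0.050 | 0.0180 | -0.085 |

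For the fourth row:

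- Means: 0.95 × 0.93 + 0.05 × 0.5 = 0.9085 and 0.95 × 0.93 + 0.05 × 0.9 = 0.9285; difference -0.020.
- Variances: 0.0706 and 0.0619; SE = √(0.0706/700 + 0.0619/350) = 0.0167.
- Lower limit: -0.020 − 0.0327 = -0.053.

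With AS+MQ held at 0.9, the limit reaches -0.050 when Artekin is at 0.55 (difference -0.0175, SE 0.0166). The tipping gap is therefore about 0.35, inside the plan's own range.

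**Step 4: standard error.** Same setting, common v:

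| v | SE, score | SE, binary | Ratio |
|---|---|---|---|
| 0.5 | 0.0174 | 0.0189 | 0.922 |
| 0.7 | 0.0166 | 0.0179 | 0.927 |
| 0.9 | 0.0163 | 0.0169 | 0.966 |

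The score SE is thus about 3-8% smaller. This can matter near the margin. With 91.5% v 93% observed cure and v = 0.7, the difference is 0.95 × (-0.015) = -0.01425. The score SE of 0.0171 gives -0.0478 (pass); the binary SE of 0.0184 gives -0.0503 (fail).

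**Step 5: what a common value does test.** Suppose 10% of Artekin and 5% of AS+MQ patients are lost (an assumption), with 93% observed cure in both arms. Then v = 0.5 gives a difference of -0.0215 and a lower limit of -0.056; Method 1 gives -0.0465 and -0.090. With the loss rates reversed, the difference becomes +0.0215 at v = 0.5.

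**The case against.** The case for the plan is substantial, and several stronger readings fail against it.

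- **A reader might infer that the robustness analyses cannot test non-informative loss, or are reassuring by construction.** They are not. Values of 0, or of 0.5 to 0.9, depart from the 93% expected among observed patients, and they penalise the arm with more loss (Step 5).
- **A reader might put Method 1 in the same class as a lenient common value.** On the lower limit it is harsher. With 91.5% v 93% cured and 5% lost in each arm, the modified ITT gives -0.0497 (pass) and Method 1 gives -0.0561 (fail).
- **A reader might see a general pull of the difference toward zero.** With equal loss, a common value multiplies the difference by (1 − L), a 5% shrinkage at the planned rate. With unequal loss, it can move the difference in either direction.
- **A reader might conclude that the co-primary populations ignore all informative dropout.** The modified ITT counts withdrawals for reasons 2 to 6 as failures. Only patients who cannot be located are dropped.
- **The text does not require one value for both arms,** and an SAP that is not shown could specify a grid. That is fair, and the point is worded accordingly. However, section 8.2.1 expressly leaves the confidence interval method to the SAP and writes the robustness methods out, so the arm contrast should be stated there or in the SAP.
- **The standard error depends on the benchmark.** If v is taken as known, the score's SE is the sampling error of that mean. Against the modified ITT's 0.0171, it runs from slightly larger (0.0174) to about 5% smaller (0.0163). The criticism is narrower: lost outcomes are not known to equal v, and at v = 0.9 adding patients without data makes the interval tighter than the modified ITT's.

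**Conclusion.** The point holds in a limited form. Both co-primary populations exclude patients lost to follow-up. The three robustness methods cover shared departures, unequal loss and non-informative censoring, but none is described as covering a departure that differs by arm.

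At the plan's own loss and cure rates, that omitted case can reverse the conclusion: -0.053 with 0.5 v 0.9, against -0.034 to -0.032 with any common value in the range. Method 2's standard error is also about 3-8% smaller than one that treats lost outcomes as binary.

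The figures rest on 5% loss in each arm, 93% observed cure in both arms, 700 and 350 patients, and a normal approximation without continuity correction. The 0.5 v 0.9 contrast is illustrative; the documents give no evidence that lost patients would differ that much. Section 3.4.2 concedes that the withdrawal rate is uncertain, and higher loss would lower the tipping gap. The primary analysis is not shown to be wrong. This should be settled before results are known.

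**What to change.** In section 8.2.1 or the SAP, amend Method 2 as follows:

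1. Vary the success probability for reason-7 patients independently in each arm over a stated grid that includes values worse for Artekin than for AS+MQ, for example 0.5 to 1.0 by arm.
2. Draw binary outcomes by multiple imputation, or use a variance that reflects the imputation.
3. Report the lower confidence limit against -0.05 for each combination, and identify those at which non-inferiority is lost.
4. Apply the same arm-specific contrast to missing or non-interpretable PCR, including failure in Artekin with success in AS+MQ.

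Keep Methods 1 and 3 and leave the primary analysis unchanged. No extra patients or data are needed. The cost is a little more analysis work, and the displayed robustness may look less favourable.
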